**Study - II**

This is a randomized controlled community trial to estimate the treatment outcome of tuberculosis patients treated by community based directly observed short course therapy. The investigator will select clusters and match for tuberculosis treatment outcome. Then will randomly allocate them to intervention and control clusters. Health workers and community health agents in the intervention clusters will receive training on community-based tuberculosis care and its implementation. They will also discuss with diagnosed tuberculosis patients about the disease and selection of treatment supervisor. Tuberculosis patients will select tuberculosis treatment supervisor from their area and discuss with health worker about their role and responsibility. Once agreed up on, tuberculosis patients will start supervised short course therapy in their community under tuberculosis treatment supervisor. The study will follow the national tuberculosis programme guideline for patient diagnosis, treatment, follow-up, recording and reporting. Patients in the non-intervention clusters will continue conventional health-facility based directly observed short course therapy.

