**Study - III**

This is a randomized controlled community trial to find out the cost per tuberculosis patient treated successfully. The study follows societal perspective of cost analysis. The main cost items related to the costs of tuberculosis prevention and control programme will be collected as for diagnosis, follow up and supervision including patient and community health workers time and costs. Data collectors will also get records from district finance offices. The data collectors will calculate cost of time based on monthly salary of health workers and tuberculosis patients if they are in the productive age groups. In addition, the cost of the person accompanying the patient will be included. The outcome indicator for the study is the cost per patient treated successfully.

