**2. Methods**

**2.1. Study design**

This is a randomized controlled community trial to find out the costs per tuberculosis patient treated successfully in the intervention and non-intervention districts. Cost related to tuberculosis control programme in the study sites will be determined according to the actual expenses and time cost. Programme coordinators, health workers, community health agents, tuberculosis treatment supervisors, tuberculosis patients and relatives accompanying them to health facilities in the study sites will be included in the study.

The cost analysis will follow societal perspective to analyse the cost per patient. The data collectors will obtain financial reports from districts and health institutions finance sections to collect expenditures for tuberculosis control programme, health workers and community health agents’ time and costs associated to tuberculosis prevention and control activities. In addition, they will collect cost of the patient and the relative who accompanied them during their visit to health institutions.

The investigator will use cost per tuberculosis patient successfully treated as an outcome measure. Future cost and productivity gains will not be included in the study. Standard cost estimation of all expenses and time of the patient, treatment supervisor and health workers will be done. Data collectors will use a structured pre-tested questionnaire for data collection.

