**2.2. Study variables**

The study variables are the socio-demographic characteristics, time, cost incurred during tuberculosis case detection, follow up and treatment. In addition cost related to supervision and monitoring and evaluation of tuberculosis control programme in the study sites will be included.

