**Cost items for treatment and follow up of the patient**

1. number of travel days _____ travel expense per day ___travel hours__
2. number of hours spent in the health institution per day ____________
3. expenses for food _______ drink ________ others with expense _____

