**Cost items for treatment supervision**

1. number of hours spent per for treatment supervision ______________
2. total number of days tuberculosis patient is supervised ____________
3. number of travel hours for drug collection _______________________
4. number of days traveled for drug collection ______________________
5. travel expenses per day _____________________________________
6. related expenses for food ___________ drink __________ others ___

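### Study III promises to cost all patient time, but the patient form has no item for time spent with the community treatment supervisor, so observed-dose contact time is recorded for control patients only

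*Protocol*

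**What the plan says.** **Scope promised in the text.** Protocol, Study Three, section 2.1 sets the viewpoint: "The cost analysis will follow societal perspective to analyse the cost per patient". It then states: "Standard cost estimation of all expenses and time of the patient, treatment supervisor and health workers will be done". Section 6.2, Study - III, lists "diagnosis, follow up and supervision including patient and community health workers time and costs" and values patient time by monthly salary for those of productive age. Study Three, section 2.2 names "time, cost incurred during tuberculosis case detection, follow up and treatment" as study variables. On what the data collectors gather from patients, section 2.1 says: "In addition, they will collect cost of the patient and the relative who accompanied them during their visit to health institutions".

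**Where doses are observed.** Under section 6.2, Study - II, in intervention clusters "tuberculosis patients will start supervised short course therapy in their community under tuberculosis treatment supervisor". Patients in the other clusters continue facility-based observed therapy.

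**What the annexed forms ask.** The treatment and follow-up block of the TB patient form has three lines: travel (days, expense, hours), "number of hours spent in the health institution per day", and food, drink and other expenses. The treatment supervisor form records hours of supervision and "total number of days tuberculosis patient is supervised".

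**The concern.** The study compares cost per successfully treated patient between randomised arms, and the arms differ in where a dose is observed. If the patient's time at that contact is asked about in one arm and has no field in the other, the same activity is priced on one side only. The text does promise the time, but time that nobody records cannot be valued at a salary.

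Patient cost is central to this study. Its sample size is built on patient cost of 30% under facility care against 13% under community care. The literature review also attributes the saving in the cited Tanzanian trial mainly to fewer clinic visits. A gap in patient time at treatment contacts therefore touches a component that the comparison depends on.

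**Working it through.** **1. The plan's own figures.** The only Study III calculation is the sample size. With z-values 1.96 and 1.28, p1 = 0.30, p2 = 0.13 and mean 0.215:

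n = (1.96 + 1.28)² × 2 × 0.215 × 0.785 / 0.17² = 122.6, rounded to 123; and 1.56 × 123 = 191.9, rounded to 192.

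Both stated figures reproduce. The point here does not depend on them.

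**2. Text against form.** The annex holds one patient cost form, and I assume that it serves both arms. Following an observed dose through the forms gives:

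| Whose time at an observed dose | Control (facility) | Intervention (community) |
|---|---|---|
| Observer | TB clinic staff form: hours for dose supervision | Treatment supervisor form: hours and days |
| Patient, contact and waiting | Patient form: hours in the health institution | No item |
| Patient, travel | Patient form: travel line | Same travel line, which names no place |

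The observer's time has a field in both arms. The patient's contact time has one only in the control arm. The walk to a supervisor might be entered on the travel line, but nothing prompts for it.

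**3. Other gaps in the same forms.** The patient's diagnosis block has no line for hours in the institution, although the block for an accompanying relative does. That relative's block covers diagnosis only, so the relative's costs at treatment visits have no field. Control patients self-report to facilities and are treated there, whereas suspects in intervention clusters give sputum in the community. These gaps therefore fall mainly on the control arm.

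**4. Size in hours (assumed inputs).** The protocol gives no minutes per dose. Assume about 60 daily doses in the first two months (2 × 30) and 2 to 30 minutes of patient time each:

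60 × 2 / 60 = 2 hours, up to 60 × 30 / 60 = 30 hours per intervention patient without a field.

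No wage or cost per arm is given, so these hours cannot be turned into cost per success.

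**5. Direction.** Let S be the saving computed from recorded costs. Let a and b be the unrecorded costs per success in the intervention and control arms, each as a share of the recorded control cost. Then

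full saving = 1 − (1 − S + a)/(1 + b) = (S + b − a)/(1 + b).

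The recorded saving is too large only if a > b(1 − S). For illustration take S = 35%, the figure quoted from the Tanzanian trial:

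- b = 0: a = 1% gives 34%, and a = 10% gives 25%.
- a = 5%, b = 0: 30%.
- a = 5%, b = 10%: 0.40/1.10 = 36.4%.

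At a = 5% the sign changes at b = 0.05/0.65 = 7.7%. Neither a nor b can be found from the protocol.

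**The case against.** A reader might infer that Study III counts patient costs only at facility visits and that the saving is therefore overstated. The protocol does not support either step.

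- The sentence about visits to health institutions opens with words of addition and contains no limiting term. The following paragraph brings all patient expenses and time into scope, and section 6.2 and Study Three, section 2.2 agree. The design as described does not exclude time in the community.
- The travel line names no place, so some community travel may be recorded.
- Patient and supervisor share the contact, so patient contact time could be derived from the supervisor's form. Charging it could be an analysis step described elsewhere.
- The forms also leave out time and costs that fall mainly on control patients, so a claim about net direction fails.
- Patients choose a supervisor from their own area, and parents may supervise children under 13, so the time could be close to nil.
- The questionnaire is to be pre-tested, which might bring the gap to light.

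All of this stands against the stronger reading. It does not remove the narrower point. A statement of scope supplies no data, the form has no line for this contact, and the protocol does not say that supervision hours will also be charged to the patient.

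**Conclusion.** The promised scope and the data collection instrument do not match. Study III undertakes to cost all patient time, but its patient form captures treatment contact time only inside a health institution. Used as written, it records observed-dose contact time for control patients and not for intervention patients. Taken alone, this lowers the intervention arm's patient time cost.

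The conclusion goes no further than that. The amount cannot be computed from the protocol; the 2 to 30 hours above rests wholly on assumed minutes and an assumed 60 doses. The net direction of bias in cost per success is unknown. The conclusion also assumes that the annexed patient form is used in both arms and that patient time is not derived from the supervisor's form. The correction is so cheap that it should be made.

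**What to change.** Do one of the following:

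- Add one line to the treatment block of the TB patient form: number of days on which doses were taken with the treatment supervisor, and hours per day including travel.
- State in Study Three, section 2.1 that the supervision hours and days on the supervisor's form are also charged as patient time, under the same salary rule. This needs no new interview item but misses the patient's own travel. In the available text the supervisor's hours item has no unit after the word per, so the unit should be confirmed first.

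The sentence on visits to health institutions needs at most a short phrase making clear that contacts with the treatment supervisor are included. It would be sensible to add the two items missing mainly on the control side in the same revision: patient hours in the institution at diagnosis, and the relative's costs at treatment visits.

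The cost of the main change is one form line or one sentence, and a slightly less favourable cost for the intervention arm. The two companion items add a few more lines to the form.

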Hence, the access to diagnostic health facilities might improve as well as the frequency of visits and cost incurred by the patients might decrease. One of the challenges to this approach is the non-adherence to the national diagnostic guidelines. [29] However, strengthening quality control system could minimize the problem. In addition, a study group in southern Ethiopia recommended regular on job training to laboratory technicians and regular supervision to improve the performance of laboratory technicians in peripheral diagnostic institutions. [30]

To be more pragmatic, implementation of tuberculosis control programme should consider the available inputs. In resource-constrained settings, programme managers opt for an intervention with low cost for improved programme indicators. Economic evaluations of tuberculosis control programme showed that treating tuberculosis is a cost-effective intervention. They further recommended additional effort to increase tuberculosis case finding and improve accessibility of service to the community in line with millennium development goals. [31]

Cost of community based tuberculosis care was determined in different countries. In Bangladesh, they compared the cost incurred by non-governmental organizations (NGOs) with that of the government for tuberculosis control programme. The NGOs used community health workers in tuberculosis case finding and patient follow-up. The cure rate was nearly equal in the two settings. However, the cost per tuberculosis patient cured by NGO was two thirds of government tuberculosis programme. The investigators recommended that collaboration with NGOs could improve tuberculosis care. However, the cost of sputum microscopy was higher than in the government programme.[32] They could also reduce the cost by strictly adhering to WHO recommendations for case finding.

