**2.4. Sample size calculation**

The treatment success rate of Sidama zone is 70 %. With the intervention, we assume effect size of 21 % so that to increase the treatment success to 85%, WHO target.

n = [(z1 + z2)*2*P]/

n = the sample size from each group z1 =level of significance of 95 %( 1.96)

z2 =power of the study of 90 %( 1.28) p1 =proportion of treatment success in control group (70%)

p2 =proportion of treatment success in intervention group (85%)

P= the average proportion of treatment success in the control and intervention groups (77.5%)

n = = = 163

IF = 1 + (m-1)*ICC

IF - inflation factor or design effect m - cluster size /15 TB patients

[Based on tuberculosis prevalence of 533 per 100,000, taking case detection rate of 47% as reported by WHO 2005, we expect 15 tuberculosis cases per village of 6000 population.]

ICC - intracluster correlation coefficient assuming typical ICC of 0.04

IF = 1 + (15 - 1) * 0.04 = 1.56 Effective sample size = IF * calculated size = 1.56 * 163 = 255

To calculate number of clusters per group

Total tuberculosis patients divided by cluster size 255 /15 = 17 clusters per group

k - Coefficient of variation = standard deviation of proportions/mean of proportions p1 = 70% p2= 85% P = 77.5% SD =0.106 k =0.12

c = 2 + /

c = 2 + / = 14 clusters

The case detection of all forms of tuberculosis is 47 % of the annual incidence of 356 cases per 105 populations. Assuming that the case detection of all forms of tuberculosis will increase to 70%, we expect case detection of 250 cases per 105 populations. Therefore, to detect 30 cases per cluster we need about 12,000 people. A Kebele /villages have a population of about 6000, in densely populated areas as in Sidama. So a cluster will have two kebeles.) With this case detection, the study will take one year for case detection and additional 6- 8 months to record treatment outcome.

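### Study III's named outcome, average cost per patient successfully treated in each arm, cannot tell a cost saving from a higher success rate, and no between-arm cost difference or incremental ratio is named

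*Protocol*

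**What the plan says.** Section 6.2 of the Protocol, under Study III, states: "The outcome indicator for the study is the cost per patient treated successfully". Study Three, section 2.1, repeats the choice: "The investigator will use cost per tuberculosis patient successfully treated as an outcome measure". The same section describes a randomised community trial whose purpose is "to find out the costs per tuberculosis patient treated successfully in the intervention and non-intervention districts", so the figure will be set side by side for the two arms.

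Cost per patient also appears, less formally. Study Three, section 2.1, says that the societal-perspective analysis concerns cost per patient, and the Summary says that cost per patient treated will be determined. Neither place makes the difference between arms an outcome. No incremental cost or incremental cost-effectiveness ratio appears in the document.

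The denominator of the named measure is the outcome of Study II. Study Two, section 2.4, gives the control rate, "The treatment success rate of Sidama zone is 70" per cent, and the target: "With the intervention, we assume effect size of 21 % so that to increase the treatment success to 85%, WHO target".

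**The concern.** A ratio of cost to successes moves when either part moves. This trial is designed to detect a large rise in success, so the ratio is expected to fall even if no money is saved per patient. It could fall while community care costs more per patient.

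Higher cost is possible. The intervention adds training, treatment supervisors' time, community health workers' time and extra supervision, all of which the cost forms collect. A reader given only two average ratios could not tell whether community care saved money, cost the same and cured more, or cost more and cured more. These are different findings for a programme with a fixed budget. The third raises a question that two averages do not answer: what each additional success costs.

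**Working it through.** **Inputs.** Control success is 70% and intervention success 85% (Study Two, section 2.4). The protocol does not define the ratio's numerator or denominator. I take it as total cost in an arm divided by successes in that arm, which equals mean cost per patient started, C, divided by the success proportion, s.

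**The plan's own figures.**
- Relative effect: 0.85/0.70 − 1 = 21.4%, matching the stated 21%.
- Study II sample size, pooled two-proportion formula: (1.96 + 1.28)² × 2 × 0.775 × 0.225 / 0.15² = 162.7, stated as 163. With the design effect, 163 × 1.56 = 254.3, stated as 255.

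The 70% and 85% are therefore the rates on which the trial is planned.

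**Equal cost per patient.** Control is C/0.70 = 1.429C per success and intervention C/0.85 = 1.176C. The relative change is 0.70/0.85 − 1 = −17.6%, whatever the value of C. The difference in cost per patient is zero.

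**Break-even.** The two ratios are equal when intervention cost divided by control cost is 0.85/0.70 = 1.214, that is, at 21.4% more per patient. This is the same number as the planned relative effect on success.

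**Worked range.** Control cost is set to 100 per patient for illustration, giving 100/0.70 = 142.9 per success. The incremental ratio is the cost difference divided by 0.85 − 0.70 = 0.15.

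| Intervention cost per patient | Cost per success | Change in ratio | Cost difference per patient | Incremental cost per extra success |
|---|---|---|---|---|
| 100 | 117.6 | −17.6% | 0 | 0 |
| 110 | 129.4 | −9.4% | +10 | 66.7 |
| 120 | 141.2 | −1.2% | +20 | 133.3 |
| 130 | 152.9 | +7.1% | +30 | 200.0 |

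In the second and third rows the ratio favours community care although every patient costs more.

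**If the target is not reached.** At equal cost, an intervention success of 75% gives 1 − 70/75 = 6.7% lower, and 80% gives 1 − 70/80 = 12.5% lower. The break-even points become 75/70 − 1 = 7.1% and 80/70 − 1 = 14.3%. With equal success the ratio changes only with cost.

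**The case against.** The strongest defence is that the outcome matches the objective. Study III's aim is worded throughout as cost per patient treated successfully. This is a recognised average cost-effectiveness ratio and includes effectiveness by design. A lower value at equal cost is a real gain. The literature review reports earlier studies on the same measure. All of that stands. However, the Tanzanian trial cited there found a 35% reduction with similar treatment outcomes, a setting in which the ratio tracks cost. This trial plans for dissimilar outcomes.

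Several stronger readings are tempting, and the document does not support them:

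- **That community care will look 18% cheaper with no saving.** This holds only if success is 70% against 85% and cost per patient is equal. The 85% is a target, and the Study III sample size assumes lower patient cost under community care (30% against 13%).
- **That cost per success is the only economic quantity planned.** Study Three, section 2.1, calls it an outcome measure and also mentions cost per patient, as does the Summary. Success by arm will be known from Study II.
- **That the protocol intends to call a lower ratio a saving, or wrongly counts the Study II effect twice.** Study III's methods say neither, and an efficiency ratio contains the effect by construction.
- **That the protocol itself asks for an incremental analysis.** Its remark that "programme managers opt for an intervention with low cost for improved programme indicators" describes cost relative to results and does not mention incremental cost.

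Two further objections also stand. The formula is inferred: if cost were averaged only over successfully treated patients, the 17.6% would not follow. And an analysis plan, not available here, may add incremental results; interval methods are commonly left to it. That does not alter which outcome the protocol names.

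**Conclusion.** The point holds in a limited form. The protocol names an average ratio as Study III's outcome in each arm and no between-arm cost comparison, in a trial planned to change the ratio's denominator. On the planning rates, and with the ratio taken as total cost over successes, it would be 17.6% lower at equal cost per patient and lower at any cost increase below 21.4%. These figures shrink if the success effect is smaller and vanish if there is none. A fall of this kind is an efficiency gain; whether it is also a saving cannot be read from the ratio. The measure is legitimate but insufficient for a randomised comparison, and the components needed to complete it are largely already planned for collection.

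**What to change.** In section 6.2 (Study III) and Study Three, section 2.1:

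1. Keep cost per success as a per-arm summary, with its numerator and denominator stated.
2. Add as comparative outcomes (a) the difference between arms in mean cost per patient started on treatment, and (b) the incremental cost per additional patient successfully treated, when both cost and success are higher under community care.
3. Show case-finding costs separately from treatment costs in (a). Study Three, section 2.2, includes the cost of case detection, and the intervention changes detection, so the number of patients started can itself differ between arms.
4. Give intervals that respect the matched clusters for costs that can be assigned to a cluster. State how shared costs are apportioned: programme costs come from district and institution finance reports, whereas Study Two, section 2.4, makes a cluster two kebeles.
5. Do not describe a lower cost per success as a cost saving unless (a) shows one.

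The cost is new wording in two places, a little more analysis, and an apportioning rule that must be written down and defended. The headline may be less favourable than a single ratio would give.
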